#### Criteria for discontinuing or modifying the intervention

2.5.4

The intervention may be discontinued or modified for an individual participant in the following circumstances: withdrawal of informed consent at any point during the trial; emergence of a severe psychiatric condition requiring specialist treatment (e.g., acute psychosis, severe depressive episode); clinically significant deterioration in psychological wellbeing as assessed by the delivering midwife and confirmed by the principal investigator; initiation of pharmacological treatment for anxiety or depression during the trial period; obstetric complications requiring hospitalisation or precluding participation; preterm birth prior to completion of the intervention; or inability to continue participation due to unforeseen personal circumstances.

In cases of discontinuation, the participant will be referred to appropriate clinical or psychological services where indicated. All outcome data collected prior to discontinuation will be retained and included in the intention-to-treat analysis. Participants who discontinue the intervention but remain willing to complete follow-up assessments will be encouraged to do so.

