#### Strategies to improve adherence and monitoring of adherence

2.5.5

Adherence will be supported through flexible scheduling in person or via secure video conferencing, provision of written session summaries and educational materials after each meeting, reminder messages prior to scheduled sessions, and telephone or message contact between sessions to maintain engagement. Partner or family involvement is encouraged where appropriate. Adherence will be monitored via a standardised session log maintained by the delivering midwife, recording the number, duration, and format of completed sessions. For the per-protocol analysis, adequate adherence is defined as completion of at least four of the six planned sessions. Reasons for non-attendance or early discontinuation will be recorded and reported.

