#### Concomitant care

2.5.6

Participants in both groups will continue to receive all routine antenatal care throughout the trial period. No concomitant structured psychological interventions or pharmacological treatments for anxiety or depression are permitted, as these constitute exclusion criteria. Use of other antenatal education resources, such as childbirth preparation classes or online informational materials, is not restricted but will be recorded at each follow-up assessment to allow for adjustment in sensitivity analyses.

The authors acknowledge that the multi-centre, multi-channel recruitment strategy—particularly the use of social media platforms and parenting forums—introduces a risk of contamination. Control participants may come into contact with intervention participants through the same online channels and consequently seek out psychoeducational support independently. This could result in an underestimation of the intervention effect. To minimise this risk, all participants will be asked at enrolment not to discuss study details with other enrolled women. At each data collection time point, control group participants will be asked whether they have used any form of psychological or psychoeducational support beyond standard antenatal care; this information will be recorded and included as a potential confounding variable in a sensitivity analysis.

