### Harms

2.7

Given the non-invasive nature of the intervention, no serious adverse events are anticipated. An adverse event is defined as any unintended negative psychological or physical experience reported by a participant during or following a session, including clinically significant increases in anxiety or acute emotional distress. Adverse events will be monitored by the delivering midwife at each session using the standardised session log and reported to the principal investigator within 24 h. Participants experiencing clinically significant deterioration will be referred to appropriate services in accordance with the safety protocol described in section Criteria for Discontinuing or Modifying the Intervention.

In cases where a participant develops severe anxiety, acute distress, or suicidal ideation, the delivering midwife will immediately notify the principal investigator, discontinue participation, and refer the participant to specialist psychiatric services. All such events will be reported to the Bioethics Committee of the Medical University of Gdańsk.

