### Statistical analysis plan

2.14

Analyses will be conducted according to randomised group allocation and will primarily follow the intention-to-treat principle, insofar as outcome data are available. The primary endpoint is PrA measured using the PRAQ-R2 at 34–37 weeks’ gestation. The primary analysis will compare post-intervention PRAQ-R2 scores between groups using analysis of covariance (ANCOVA), with treatment group as the main factor and baseline PRAQ-R2 score as a covariate. The primary outcome is assessed at two prenatal time points only: baseline and post-intervention. The postpartum assessment applies exclusively to secondary outcomes.

Secondary outcomes will be analysed using regression models appropriate to outcome type, with logistic regression for binary outcomes and linear regression for continuous outcomes. Secondary analyses will be considered supportive and exploratory; no formal adjustment for multiplicity is planned. Missing data will be described by study arm and time point. The primary analysis assumes data are missing at random (MAR); this assumption will be examined via sensitivity analysis, using a mixed-effects model for repeated measures applied to all available longitudinal data. Multiple imputation is not planned. The possibility of data missing not at random (MNAR) cannot be excluded and is acknowledged as a limitation. Stratification variables included in the randomisation will be entered as covariates in the primary ANCOVA model. A supportive per-protocol analysis will also be conducted among participants with observed primary endpoint data; in the intervention arm, this will additionally require completion of at least four intervention sessions. Two pre-specified sensitivity analyses will be conducted: (1) a linear mixed-effects model including midwife as a random effect, to account for potential clustering by intervention deliverer; and (2) a mixed-effects model for repeated measures applied to all available longitudinal data under a missing-at-random assumption, to assess the robustness of findings in the presence of incomplete data.

The mode of intervention delivery (in-person versus remote) will be recorded. As the trial is not powered for formal moderator analyses, any comparison by delivery mode will be considered exploratory and interpreted cautiously.

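### The supportive per-protocol set filters on attendance in the intervention arm only, so it can select on outcome in one arm and would probably favour the intervention

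*Protocol article*

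**What the plan says.** Section 2.14 defines the set in one sentence. The condition for both arms is an observed Time II score: "A supportive per-protocol analysis will also be conducted among participants with observed primary endpoint data". The further condition is for one arm: "in the intervention arm, this will additionally require completion of at least four intervention sessions". Section 2.5.5 gives the same threshold for this analysis: "adequate adherence is defined as completion of at least four of the six planned sessions". Neither section sets a condition for controls beyond the observed endpoint. The article states that it contains the full statistical analysis plan, so this is the definition itself and not a summary of one held elsewhere.

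Section 2.5.4 lists the circumstances in which a woman's sessions may be stopped or changed. They include "clinically significant deterioration in psychological wellbeing as assessed by the delivering midwife and confirmed by the principal investigator" and "initiation of pharmacological treatment for anxiety or depression during the trial period". Section 2.7 adds that, for severe anxiety, distress or suicidal thoughts, "the delivering midwife will immediately notify the principal investigator, discontinue participation, and refer the participant to specialist psychiatric services". Section 2.5.4 also encourages women who stop the intervention to complete follow-up, so some early stoppers should have a Time II score.

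**The concern.** The primary outcome is anxiety, and several of the protocol's own reasons for ending sessions are worsening anxiety or close relatives of it. A woman who worsens, stops after two or three sessions and still completes the Time II questionnaire leaves the per-protocol set. A control woman who worsens in the same way has no sessions to miss and no delivering midwife to stop them, so she stays in. The comparison is then between a selected intervention arm and an unselected control arm, and adjustment for baseline PRAQ-R2 does not remove selection on what happened after randomisation.

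What is at stake is how a secondary result is read. Section 2.9 says the trial is meant to give an initial effect estimate for a larger one. If the primary result is weak and the per-protocol result is larger, it invites the reading that the programme works when women attend. This comparison cannot support that reading.

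**Working it through.** The plan states no figure for this analysis set, so there is none to reproduce. The check has two steps.

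**1. Who is removed, among women with a Time II score**

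| Event | Intervention arm | Control arm |
|---|---|---|
| Deteriorates, fewer than four sessions | removed | kept |
| Starts anxiety or depression medication, fewer than four sessions | removed | kept |
| The same events after session four | kept | kept |

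Women without a Time II score are absent from both arms. The asymmetry therefore concerns women who have a score and stop before session four.

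**2. How large the distortion could be if there is no true effect**

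Inputs from section 2.9: 37 women per arm, SD 8.56, planned effect 3.27 points, two-sided 5% level. The model is the ANCOVA of section 2.14.

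Assumed inputs, because the article gives none:
- p, the share of the intervention arm removed: 10% or 20% (37 × 0.10 = 3.7 and 37 × 0.20 = 7.4 women).
- ρ, the correlation between the tendency to stop and the baseline-adjusted Time II score: 0, 0.3 or 0.6.
- r, the baseline to Time II correlation: 0.5 or 0.84. The upper value is what 31 per arm would need with these inputs: 2 × (8.56 × 2.80 / 3.27)² ≈ 107.6 per arm without adjustment, and √(1 − 31/107.6) ≈ 0.84.

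Closed form: bias = −ρ × SD × √(1 − r²) × φ(z) / (1 − p), where z is the (1 − p) normal quantile. A negative value favours the intervention.

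- φ(z)/(1 − p) is 0.1755/0.9 = 0.195 at p = 10% and 0.280/0.8 = 0.350 at p = 20%.
- Residual SD is 8.56 × 0.866 = 7.41 at r = 0.5 and 8.56 × 0.543 = 4.64 at r = 0.84.
- Smallest non-zero case: 0.3 × 4.64 × 0.195 = 0.27 points.
- Largest case: 0.6 × 7.41 × 0.350 = 1.56 points.

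The type I error comes from simulating the ANCOVA with baseline truncated to 30–50 (3,000 runs per row):

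| p | ρ | r | Closed-form bias | Simulated bias | Type I error |
|---|---|---|---|---|---|
| 10% | 0.3 | 0.84 | −0.27 | −0.29 | 0.064 |
| 10% | 0.3 | 0.5 | −0.43 | −0.43 | 0.049 |
| 10% | 0.6 | 0.84 | −0.54 | −0.54 | 0.079 |
| 10% | 0.6 | 0.5 | −0.87 | −0.91 | 0.086 |
| 20% | 0.3 | 0.84 | −0.49 | −0.50 | 0.070 |
| 20% | 0.3 | 0.5 | −0.78 | −0.86 | 0.063 |
| 20% | 0.6 | 0.84 | −0.98 | −0.98 | 0.129 |
| 20% | 0.6 | 0.5 | −1.56 | −1.50 | 0.124 |

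Against the planned effect, 0.27/3.27 = 8% and 1.56/3.27 = 48%. With ρ = 0 the bias is zero. When the same selection was applied to both arms, the mean difference stayed within about 0.1 point of zero and the type I error was 0.039 to 0.055.

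**The case against.** Attendance can only be required in the arm that has sessions, and this analysis is pre-specified, called supportive and ranked below the primary ANCOVA. That is true, and it limits the consequence. It does not make the comparison unbiased.

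The direction is not proven. Section 2.5.4 says only that sessions may be discontinued or modified. It also lists reasons with no obvious link to anxiety, such as withdrawal of consent and personal circumstances. Women recruited at 29–30 weeks could fall short of four sessions through scheduling alone, and women who stop because they feel better would push the bias the other way. Some women discontinued under section 2.7 may give no Time II score, which would touch the primary analysis as well. All of this stands, and it is why the claim is limited to a probable direction.

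The size is also assumed. A reader might take the 20% allowance in section 2.9 as the share removed, but that allowance also covers women with no usable endpoint. The group that matters here has a Time II score and fewer than four sessions, and no rate is given for it.

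A stronger reading is tempting. Section 2.5.6 says: "No concomitant structured psychological interventions or pharmacological treatments for anxiety or depression are permitted, as these constitute exclusion criteria". The per-protocol set does not apply this rule, and a reader might infer that this too tilts the result toward the intervention. The documents do not support that. The set ignores such treatment in both arms alike. Section 2.5.6 already plans a sensitivity analysis for extra support used by controls, and it says that contamination could make the effect look smaller.

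**Conclusion.** The point holds in limited form. The one-arm attendance rule is stated outright, and the protocol's own stopping grounds give a route by which it can select on outcome. The probable direction favours the intervention, on the assumption that women who worsen are more likely to stop before session four. Under the assumed ranges the spurious benefit is roughly 0.3 to 1.6 points, with type I error of about 5% to 13%; it is nil if stopping is unrelated to outcome. A reader might infer that the analysis is designed to favour the programme or is bound to inflate the effect. Neither follows from the text. The primary comparison, the sample size and the main conclusion are unaffected. The change is worth making because it costs little and the present analysis does not estimate the effect of receiving the programme.

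**What to change.** In section 2.14, make the supportive adherence analysis a complier-average causal effect: two-stage least squares with randomised arm as instrument, baseline PRAQ-R2 as covariate, and every woman with a Time II score in both arms. Use completion of at least four sessions as the exposure, and add a second version with number of sessions attended. The session logs in section 2.5.5 already hold the data, and the method fits because the programme is offered only in the intervention arm.

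State two limits:
- The four-session version assumes that one to three sessions have no effect. If they help by d points, it overstates the effect: with 20% of the arm below four sessions, by 0.2/0.8 × d = 0.25d.
- The interval is wider. With 80% completing, the standard error is about 1/0.8 = 1.25 times that of the comparison by randomised arm.

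If the per-protocol table is kept, label it descriptive and say that it may be biased by selection in one arm. The cost is a few sentences and a few lines of code, with no new data.

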### Data monitoring and trial monitoring

2.15

No independent data monitoring committee (DMC) has been established for this trial, given the small sample size, the non-invasive and low-risk nature of the psychoeducational intervention, and the absence of planned interim analyses. Safety monitoring and trial conduct will be overseen by the principal investigator throughout the study period, including regular review of recruitment progress, adherence to the intervention protocol, completeness of data collection, and adverse event reporting in accordance with the procedures described in section Harms.

## Ethics

3

This trial was approved by the Bioethics Committee of the Medical University of Gdańsk (KB/367/2025, KB/20/2025, KB/20–80/2026) and will be conducted in accordance with the 1964 Declaration of Helsinki. Any important protocol amendments will be submitted to the Bioethics Committee prior to implementation and reported to the trial registry. Women meeting the eligibility criteria will receive written study information and will be encouraged to ask questions before deciding to participate. Electronic informed consent will be obtained from all participants prior to inclusion. Participants may withdraw at any time without justification or consequences for their clinical care. All personal data will be handled in accordance with GDPR. Adverse events will be monitored and reported as described in section Harms. No compensation or post-trial care provisions are applicable given the non-invasive nature of the intervention.

## Discussion

4

This study protocol describes a planned randomised controlled trial aimed at evaluating the effectiveness of an individualised psychoeducational programme delivered by midwives. The programme is designed to reduce PrA and reduce the preference for caesarean section in the absence of medical indications among pregnant women in Poland who are at low risk of complications. The intervention is based on patient empowerment, education and emotional support, and aims to fill a significant gap in perinatal mental healthcare in a country where caesarean section rates are exceptionally high (64).

The rationale for this intervention is robust, supported by growing scientific evidence indicating that pregnancy-related anxiety constitutes a distinct and significant health concern. Unlike generalised anxiety, PrA focuses on specific aspects of pregnancy, such as foetal health, labour pain and maternal competence, making it particularly amenable to targeted psychoeducation. The intervention structure corresponds to recommended components of programmes designed to reduce fear of childbirth. It ranges from initial assessment and relationship-building, through education on childbirth physiology and pain management, to communication skills and birth planning. By equipping women with knowledge and practical coping strategies, the intervention aims to enhance their sense of control and self-efficacy, which are key psychological factors in mitigating PrA.

The selection of midwives to deliver the intervention is deliberate and holds particular significance in the Polish context. The Polish perinatal care system is characterised by a high degree of medicalisation and fragmentation, which often leaves women feeling disempowered regarding the course of their pregnancy and childbirth, thereby intensifying their anxiety. Midwives, owing to their specialised knowledge of physiological pregnancy and childbirth, are ideally positioned to provide continuity of care, woman-centred communication, and support that does not pathologize natural processes. Training midwives in structured psychoeducational techniques—without requiring advanced psychotherapeutic qualifications—enhances the intervention’s scalability and potential for integration into standard prenatal care pathways. This approach aligns with the guidelines proposed by the World Health Organization (WHO), which recommend non-pharmacological interventions to reduce unnecessary caesarean sections, particularly through addressing maternal anxiety (29).

This approach is further validated by recent evidence from Padilla et al., who demonstrated that online group prenatal education delivered by midwives significantly reduced fear of childbirth in women with high levels of fear (mean difference = 22.74 points, *p* < 0.001). Their intervention—based on self-care deficit theory and consisting of five weekly videoconferencing sessions—also showed trends towards improved obstetric outcomes, including higher rates of spontaneous labour onset (65). Importantly, this was among the first midwife-led trials to evaluate a comprehensive intervention spanning both prenatal and intrapartum periods, demonstrating the feasibility and effectiveness of midwife-delivered psychoeducational programmes in routine prenatal care settings. It should be noted that the effect size reported by Padilla et al. is not directly comparable to the effect estimate used in the present power calculation, as the two studies differ in measurement instruments, intervention format, and comparison conditions. The present trial was powered based on Polish normative PRAQ-R2 data, adopting a conservative estimate to ensure robustness of the sample size calculation.

The evaluation of this intervention may additionally contribute to reducing the rate of medically unjustified caesarean sections by addressing one of their key psychological determinants. Should the trial demonstrate effectiveness, the implications would be two-fold. First of all, it would provide an evidence-based, practical tool for addressing the rising caesarean section rates in Poland—a public health crisis. By reducing the anxiety-driven demand for elective surgical procedures, the intervention could contribute to lowering procedural rates to WHO-recommended levels, thereby reducing associated maternal and neonatal morbidity. Secondly, it would validate a care model that strengthens the role of midwives as autonomous providers of psychological support, potentially informing health policy changes towards more holistic and continuous midwifery-led care models in Poland.

The transferability of findings to other healthcare contexts should, however, be considered carefully. The present intervention is embedded within a specific Polish perinatal care context, characterised by high medicalisation, limited midwifery autonomy, and fragmented continuity of care. Countries with similar structural characteristics—including high caesarean section rates driven by non-medical factors, restricted access to midwife-led care, and comparable cultural attitudes towards childbirth—may represent the most appropriate settings for replication. By contrast, healthcare systems with well-established midwifery continuity models, routine psychosocial screening, or lower baseline anxiety levels may yield different effect sizes. Additionally, cultural norms surrounding mental health, help-seeking behaviour, and the perceived role of midwives in psychological support vary considerably across countries and should be accounted for when adapting this intervention to new contexts.

Should the trial fail to demonstrate a statistically significant reduction in PrA, this would itself constitute a scientifically valuable finding. A null result would suggest that the individualised midwife-led psychoeducational format, as implemented in this protocol, may not be sufficient to produce measurable anxiety reduction within the studied population and timeframe. Such a finding would prompt reconsideration of the intervention intensity, session frequency, or target population, and could redirect future research towards alternative formats, such as group-based interventions or those incorporating psychological specialist support. From a policy perspective, a null result would caution against large-scale implementation of this specific model without further evidence, while still supporting the broader agenda of integrating mental health screening into routine antenatal care in Poland.

The potential limitations of this study must be acknowledged. Reliance on self-report measures for the primary outcome, despite using a validated instrument (PRAQ-R2), introduces the possibility of reporting bias. The sample, recruited based on high PrA scores and Polish language proficiency, may not be fully representative of the entire pregnant population. Furthermore, intervention effectiveness may depend on the skills and consistency of individual midwives, despite standardised training and fidelity monitoring. Although variability in intervention delivery across midwives is acknowledged as a limitation, this will be statistically addressed by including midwife as a random effect in a mixed-effects model, thereby accounting for clustering within deliverers. Nevertheless, residual variability in therapeutic style, communication approach, and professional experience cannot be fully eliminated and may influence participant outcomes. The control group receiving “standard care” may experience varying levels of support, though provision of a basic informational booklet aims to partially address ethical concerns and somewhat standardise this aspect.

Several additional limitations should be acknowledged. First, the booklet-only control condition does not constitute an active comparator, which precludes conclusions about which specific components of the psychoeducational intervention are therapeutically active; a dismantling study would be required to address this question. Second, the primary outcome is assessed at 34–37 weeks of gestation, a period during which anxiety levels may naturally fluctuate due to proximity to childbirth, independent of any intervention effect; this third-trimester confound cannot be fully disentangled from intervention-related change. Third, the postpartum data collection window is defined as six or more weeks after birth, which may introduce heterogeneity in outcome measurement due to variability in the timing of assessments across participants; future studies should consider a more precisely defined postpartum assessment window. The primary outcome is assessed immediately following intervention completion, which does not permit evaluation of effect durability. An additional assessment at 38–40 weeks was considered but deemed unfeasible due to participant burden in late pregnancy and logistical constraints in scheduling prior to delivery; this is recommended as a priority for future trials.

Furthermore, the multi-channel recruitment strategy—encompassing public antenatal clinics, childbirth education schools, and online platforms—may result in a heterogeneous study population. Women recruited through different settings may differ systematically in health literacy, sociodemographic characteristics, and anxiety profiles. Although recruitment source will be recorded and included as a covariate in sensitivity analyses if meaningful imbalances are identified, residual differences between subgroups cannot be fully eliminated and may limit the generalisability of findings. The restriction to women scoring ≥30 on the PRAQ-R2—a pragmatic threshold based on Polish normative data rather than a validated clinical cut-off—limits generalisability to women with lower but potentially clinically relevant anxiety levels. Reasons for screening refusal will be recorded where possible and reported in the CONSORT flow diagram to allow assessment of selection bias.

Future research stemming from this trial could be focused on examining the long-term effects of the intervention on maternal mental health (e.g., postpartum depression, bonding), infant health outcomes and the sustainability of birth mode decisions in subsequent pregnancies. Cost-effectiveness analyses would be crucial for promoting wider implementation within the public healthcare system. Additionally, qualitative studies exploring the experiences of both women and midwives participating in the programme could provide valuable insights for refining the intervention and understanding its mechanisms of action.

